## Abstract

**Background:** Improving the quality of care for people with vascular disease is a key priority. Chronic kidney disease (CKD) has recently been included as a target condition for general practices to add to registers of chronic conditions as part of the Quality and Outcome Framework. This paper outlines the implementation and evaluation of a self-management intervention involving an information guidebook, tailored access to local resources and telephone support for people with stage 3 chronic kidney disease.

**Methods/Design:** The study involves a multi-site, longitudinal patient-level randomized controlled trial. The study will evaluate the clinical use and cost-effectiveness of a complex self-management intervention for people with stage 3 chronic kidney disease in terms of self-management capacity, health-related quality of life and blood pressure control compared to care as usual. We describe the methods of the patient-level randomized controlled trial.

**Discussion:** The management of chronic kidney disease is a developing area of research. The BRinging Information and Guided Help Together (BRIGHT) trial aims to provide evidence that a complementary package of support for people with vascular disease that targets both clinical and social need broadens the opportunities of self-management support by addressing problems related to social disadvantage.

**Trial registration:** Trial registration reference: ISRCTN45433299

**Keywords:** Vascular disease, Chronic kidney disease, Self-management, Randomized controlled trial, Social disadvantage, Social networks, Social prescribing, Minimally disruptive medicine

\* Correspondence: [contact]

Centre for Primary Care, Institute of Population Health, University of Manchester, [name]

Full list of author information is available at the end of the article

## Background

Vascular disease is the largest single cause of long-term ill health and disability in the United Kingdom and disproportionately affects socially disadvantaged populations [1,2]. Providing effective self-management support is a key policy focus which aims to improve the skills and confidence of patients to manage their illness. However, existing approaches to supporting self-management have shown limitations, particularly with equivocal evidence in outcomes for socially disadvantaged groups [3-5]. The limitations of these approaches to self-management support strategies are that they over-simplify the everyday challenges faced by people living with long-term health problems and have often overlooked the social and structural barriers such as access to resources, identifying needs appropriately, and the role of personal networks of support [3,4,6,7].

The BRinging Information and Guided Help Together (BRIGHT) intervention aims to address this implementation gap and recognizes a necessity for changes to be made at the level of the patient, practice, organization and community [7-12]. With a particular need to address the interface between primary care and resources in the community, the BRIGHT intervention intends to enhance the effectiveness of self-management strategies by focusing more on patient contexts and personal networks that are centrally involved in the mobilization and deployment of resources used in managing chronic disease [13].

The BRIGHT intervention aims to improve the care and outcomes for people with vascular conditions, in particular stage 3 CKD, by:

1. Providing patient information that incorporates both clinical and lay-experiential knowledge.
2. Broadening the scope of self-management support to address both social and clinical needs.
3. Linking patients' needs and preferences to local community resources.
4. Embedding strategies for self-management support into existing approaches to the delivery of care for patients with long-term conditions.

This approach builds on evidence that socially disadvantaged groups may benefit from interventions which are lay-led and community-located [2,4] and builds on evidence that social networks are implicated in self-care support outside formal health services [6]. A shift in emphasis from an exclusive focus on the individual is required to one which includes a greater focus on the mobilization of resources and interaction with aspects of everyday life (for example, home, family, work, leisure and friends). Therefore the aim of the BRIGHT intervention is to elicit people's needs in order to develop social support strategies that can be

added to existing evidence-based approaches to guided self-management support [13].

## Developing a patient information resource

The BRIGHT intervention aims to improve self-management support for people with vascular disease by addressing an identified gap in the provision of information for patients with stage 3 chronic kidney disease (CKD) [14]. A self-management guidebook was developed for this trial entitled 'Keeping your Kidneys Healthy - a guide to help you understand and manage the early stages of kidney problems'. The development of the guidebook followed principles which have been established as part of a whole systems approach to the provision of self-management support [8,15-18]. These are: lay informed experiences to be given equal weight to medical and clinical informed evidence; the inclusion of personal experiences and anecdotes to bring the information alive and; information which is based on patient's expressed needs and actual ways of managing and not on assumptions. Further principles followed included: good design; use of plain English; and use of clear diagrams, pictures and cartoons to aid understanding. The content includes and acknowledges areas of uncertainty or lack of evidence to encourage people to think about how they currently manage their condition, what they want to change, and plan how to make changes by themselves using the support of family and friends or working with their doctor or nurse.

Provision of meaningful information around stage 3 CKD may provide a platform for improved medicines management and lifestyle change [19]. CKD is common, is associated with lower socioeconomic status, and often exists with other conditions such as hypertension, diabetes and ischemic heart disease [20-24]. CKD is an independent risk factor for cardiovascular disease and its early recognition and treatment, targeted at reducing blood pressure can prevent or delay progression and reduce the risk of cardiovascular disease and renal failure [25,26]. However, stage 3 CKD is usually asymptomatic and awareness of diagnosis is low [27].

Professionals have expressed concerns that disclosing asymptomatic stage 3 CKD to patients may create anxiety, particularly 'in the 'elderly' and those in whom clinical benefit is deemed less certain [14]. General practitioners (GPs) and practice nurses may not always disclose a diagnosis of CKD to patients as the condition and its associated risks are considered difficult for patients to understand [28]. Furthermore, most qualitative studies on experiences of managing kidney disease have focused on end stage renal failure and dialysis [29,30]. Taking these concerns into account, the BRIGHT intervention aims to improve the delivery of vascular care through the provision of an information resource as a key component of a complex self-management intervention for patients

diagnosed with stage 3 CKD. The guidebook was developed to address a tendency to avoid information exchange around CKD and the approach taken aims to avoid treating stage 3 CKD in isolation but rather recognizes its management in the context of everyday life and in which maintaining health while living with multiple conditions is the norm rather than the exception [31].

**Broadening the scope of self-management support: linking patients’ needs and preferences to local community resources**

The BRIGHT intervention draws on the notion of ‘social prescribing’ which is a recent initiative embracing an approach to support for people with long-term health problems that links clinical, everyday and personal contexts. Social prescribing is a link scheme between primary care and the community and voluntary sector which provides pathways for patients to access acceptable and available community support [32-35]. There is some evidence that this approach can reduce isolation in patients, increase the confidence of patients to manage their health and improve the patient-clinician consultation by providing alternative community-based options of support for patients, which are acceptable and tailored to specific needs [32,34]. However uncertainties persist about optimal ways to refer patients from primary care into community and voluntary sector organizations because clinicians are either unaware of existing services or are unclear about how they meet the clinical needs of patients.

**Embedding self-management support strategies into current delivery of care**

The BRIGHT intervention has been informed by Normalization Process Theory (NPT), which provides a framework to understand and address processes underpinning existing delivery of care [36,37]. The study embraces the concept of *minimally disruptive medicine*, which focuses on improving health outcomes through provision of services that are designed to enhance individual capacity to manage health and reduce the burden of treatment on people’s lives [38]. This approach includes prioritizing care from the patient’s perspective, addressing coordination between services, as well as acknowledging multimorbidity in both the design of care delivery and development of an evidence base. The BRIGHT intervention has therefore been designed to build on dialogue between primary care clinicians and patients.

The BRIGHT trial aims to provide evidence that a complementary package of support for people with vascular disease which targets both clinical and social needs can broaden the scope of self-management support by addressing problems related to social disadvantage [33,34]. In summary, the BRIGHT intervention builds on the evidence in Table 1.

**Table 1 Components of the BRinging Information and Guided Help Together (BRIGHT) intervention**

| Evidence                                                                                                                                                                                            | Component of the BRIGHT intervention                                                                                              |
|-----------------------------------------------------------------------------------------------------------------------------------------------------------------------------------------------------|-----------------------------------------------------------------------------------------------------------------------------------|
| Information can be an effective platform for changing behavior and can be improved by integrating patient experience alongside medical information about management and treatment [4,15-17].        | A kidney information guidebook for people with stage 3 CKD.                                                                       |
| Social prescribing has shown encouraging results at improving health outcomes, reducing social isolation and improving the quality of the clinical consultation [35].                               | A self-assessment questionnaire which is linked to an interactive website to tailor access to types of community-based resources. |
| Socially disadvantaged groups are more likely to benefit from interventions that fit with patients’ existing adaptations and that reduce social isolation and improve access to resources [3-6,39]. | A telephone consultation with a support coordinator to guide patients through the questionnaire and website.                      |

Our approach for the design and proposed evaluation of the BRIGHT complex intervention follows guidance as outlined by the Medical Research Council [40]. We are developing an evidence base for the BRIGHT intervention using a mixed methodology combination of a randomized controlled trial (RCT), nested qualitative research and economic evaluation.

**Aims**

The principal research question is: In patients with stage 3 chronic kidney disease, can a complex self-management intervention to improve knowledge of CKD management and promote links with local community resources improve self-management capacity, health-related quality of life and blood pressure control compared to care as usual?

**Methods/Designs**

**Design overview**

The study is a two-arm, patient-randomized, RCT. Participants will be primary care patients registered with general practices with an existing diagnosis of stage 3 CKD. Participants will be allocated to one of two groups: an intervention group or a control group. The intervention group will receive the BRIGHT intervention, to be delivered after a recent clinical appointment with a GP or practice nurse. Participants in the control group will receive care as usual from their general practice and will be provided with the guidebook and website link at the end of the trial. Patient data will be collected at two time points: at baseline (prior to group allocation and intervention delivery) and at six months post-intervention. The reporting of this trial follows the Consolidated Standards of Reporting Trials (CONSORT) guidelines [41-43].

**Population**

Patients must have a clinical diagnosis of stage 3 CKD and will be identified from disease registers at GP practices. Patients must be able to communicate in English and there will be agreement with practices that the patient is appropriate to be recruited to the trial. Patients receiving palliative care or who have reduced capacity to consent will be excluded from the trial.

Inclusion criteria will be stage 3 chronic kidney disease (both stages 3a and 3b).

Exclusion criteria will be: mental incapacity to provide informed consent; inability to communicate in English; receiving palliative care. Only one person per household will be eligible for the study to avoid potential contamination between control and intervention patients.

**Intervention**

The proposed intervention entails provision of:

- 1. A kidney information guidebook.
- 2. A PLANS booklet and access to an interactive website with tailored access to local resources.
- 3. Telephone support from a dedicated peer support worker (see Figure 1).

**The guidebook**

The kidney information guidebook builds on previous research conducted by the authors, which shows that health information is an effective strategy to support self-management and can be improved by incorporating the views and experiences of patients with clinical guidance about management and treatment [4,15-17,44].

Two focus groups of patients with stage 3 CKD were conducted and were recorded, transcribed and analyzed. The guidebook was then developed using the empirical data and qualitative literature. It includes sections on patient experience, self-management options and techniques, and the uncertainties and complexities of

living with long-term conditions. The guidebook also includes basic information about the early stages of kidney problems and how they are managed by the health service. The development process included input and feedback from clinicians on the clinical guidance included in the guidebook.

**PLANS booklet and website**

PLANS (Patient-Led Assessment for Network Support) is an intervention developed from empirical work conducted by this center with patients with vascular disease that aims to increase social contact and promote community support and engagement by creating links with local resources based on need and personal preference. PLANS is a patient self-assessment tool which links patients with vascular disease to relevant local health resources. PLANS aims to support sustainable health choices by promoting local resources that are both acceptable and accessible to patients. The resources in the PLANS database fall into one or more different categories (see Table 2).

Patients receiving the intervention will have access to the PLANS website and a PLANS booklet will be available for patients without internet access. Both the website and the booklet contain the same information. The telephone support facility will guide participants through the PLANS questions and options on the database.

**Telephone support**

Self-management interventions built around structured telephone support offer a mechanism to reach patients who have poor access to health care. Evidence indicates telephone-based support in patients with associated vascular conditions improves patient outcomes, such as social support [45,46], and reduces hospitalizations [47,48].

**Table 2 PLANS categories**

| Category                                | Description                                                                                                                                                 |
|-----------------------------------------|-------------------------------------------------------------------------------------------------------------------------------------------------------------|
| Well-being                       | Groups, services and activities intended for general well-being and social participation (for example, hobbies and interest groups).                        |
| Health education                 | Groups, services and activities that offer health related advice, guidance and support such as healthy eating or condition-specific support.                |
| Practical support                | Groups, services and activities that offer everyday practical support (for example, day care and adult respite and home support such as handyman services). |
| Diet, cookery and healthy eating | Groups, services and activities that offer support and guidance for diet and healthy eating (for example, slimming groups).                                 |
| Exercise and physical activity   | Groups, services and activities that provide opportunities to keep fit and participate in physical activity (for example, sports clubs or walking groups).  |
| Mobility                         | Services that offer support for people with limited mobility or have difficulty using public transport (for example, shopping and delivery services).       |

[figure not shown]

**Figure 1 BRINGing Information and Guided Help Together (BRIGHT) Intervention.**

Non-health care professionals, such as 'peers', are increasingly being used to offer telephone support as an alternative form of support from that offered by clinicians to reach disadvantaged populations and to provide more efficient delivery of care [39,49,50]. Peer telephone support may have potential as a cost-effective intervention [51,52]. Evidence suggests that peer telephone support produces better health outcomes including effects on self-management behavior for patients with associated vascular conditions [46,48,49,53].

As part of BRIGHT we will recruit peer volunteers (or lay workers), to deliver structured telephone support to all patients in the intervention group. Peer support workers will participate in a three-hour training session to clarify and review evidence-based content materials required for effective structured telephone support [49,54], and to clarify when and how to facilitate appropriate referrals to local resources. To facilitate training, peer support workers will develop a detailed workbook and receive guidance on how to deliver the intervention by telephone.

Patients in the intervention group will receive two telephone calls from a dedicated peer support worker; one call at one-week post-administration of the kidney information guidebook and the PLANS booklet, followed by another call at four-weeks post-intervention. A peer support worker will guide the patient through options for local organizations and activities using motivational techniques over the telephone. Additionally, patients will be able to discuss alternative options for maintaining general vascular health, lifestyle and self-management support (for example, diabetes-specific education programs) with a peer support worker. Peer telephone support will be made available (Monday to Friday) throughout the course of the trial for ongoing contact by participants, should they require further assistance in linking to community resources.

## Outcomes

All outcomes are at the level of the patient. The primary end-point will be the six-month follow-up for patient health outcomes and costs. The trial has three primary outcomes: one clinical outcome of blood pressure control (dichotomized as controlled versus not controlled) and two patient-reported outcomes of 1) self-management ability, and 2) health-related quality of life (see Additional file 1). Secondary outcomes include additional measures of self-management ability, health status, anxiety (general and CKD-specific), loneliness, medication adherence, social networks and social involvement. Information on service utilization and resource use will also be collected for use in a cost-effectiveness analysis (see below). Each patient will complete a baseline questionnaire, and a follow-up questionnaire will be sent at six months (see Additional file 1).

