### Sample size calculation

The study is designed to have 80% power to detect a standardized effect size of 0.25 on the primary outcome of self-management between the control and intervention arms. This is a relatively small effect, but is in line with most sizes of effect observed in our previous trials of self-management interventions. Using an alpha of 0.05, and assuming a correlation of 0.5 between outcome measures at baseline and follow-up (a conservative estimate), and 25% attrition of participants, we will recruit 500 patients across both arms of the trial. We aim to recruit 16 to 18 practices and to recruit 28 to 32 patients from each practice.

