### Analysis

For each of the outcomes, multilevel regression analysis will be used to examine differences between trial arms.

For binary outcomes (for example, BP control) the model will be logistic regression; for continuous outcomes the model will be linear regression. All analyses will follow intention-to-treat principles and a pre-specified analysis plan. Primary analyses will control for baseline scores and the design factors (practice, age-group, smoking status, and additional vascular disease). Where appropriate, sensitivity analyses will be conducted (for example, treating all missing BP data as failures; control for additional covariates; bootstrapped *P* values for skewed outcomes). All analysis will be undertaken using Stata version 12 (<http://www.stata.com>) and an alpha level of 5%. In the case of missing data values, we will apply mean imputation and regression imputation where rates are low, and consider multiple imputation where they exceed 10%.

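### Three equal-rank primary outcomes, a flat 5% alpha and power stated for only one of them, with no rule for what counts as success

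*Protocol*

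**What the plan says.** Four sections of the protocol bear on this.

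- **Aims.** The principal question is whether the intervention can "improve self-management capacity, health-related quality of life and blood pressure control compared to care as usual". The three are joined by a conjunction, but no decision rule follows.
- **Outcomes.** "The trial has three primary outcomes: one clinical outcome of blood pressure control (dichotomized as controlled versus not controlled) and two patient-reported outcomes". The two patient-reported ones are self-management ability and health-related quality of life. All are assessed at six months and none is ranked above the others.
- **Sample size calculation.** The trial is designed for "80% power to detect a standardized effect size of 0.25 on the primary outcome of self-management". The calculation proceeds "Using an alpha of 0.05". No power is given for quality of life or blood pressure control.
- **Analysis.** For every outcome, "multilevel regression analysis will be used to examine differences between trial arms". The level for all analysis is given as "an alpha level of 5" per cent. There is no split, order, gatekeeping or adjustment. The section also refers to a pre-specified analysis plan, which is not at hand.

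**The concern.** An alpha and a power describe a trial only once it is clear what the trial must show. Here the Outcomes section names three primary outcomes, while the sample size spends the full 5% on one of them. If one significant result is enough, 5% is the error rate of each test and not of the trial. If all three are needed, 80% is the power of one component and not of the trial.

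The outcomes differ in kind: one binary clinical measure and two questionnaire scores. A mixed result is therefore quite possible. Without a rule, the headline could be chosen after the results are known, and a single chance finding could be presented as success on a primary outcome.

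**Working it through.** **Inputs from the protocol.** Three primary outcomes (Outcomes); alpha 0.05 (Sample size calculation, Analysis); power 80%, standardized effect 0.25, baseline to follow-up correlation 0.5, attrition 25%, N = 500 (Sample size calculation); adjustment for baseline scores (Analysis).

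**Assumptions, because the protocol does not give them.** Two-sided tests, 1:1 allocation, and test statistics that are jointly normal with a common correlation, shown over a range.

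**1. Reproduce the plan's own figure.** With baseline adjustment the residual variance is 1 − 0.5² = 0.75.

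- n per arm = 2 × 0.75 × (1.960 + 0.842)² / 0.25² = 188.4, rounded up to 189, so 378 completers.
- 378 / 0.75 = 504 (502.3 without rounding), against the stated 500.
- Power with 500 × 0.75 / 2 = 187.5 per arm: the standard error is √(2 × 0.75 / 187.5) = 0.0894, and 0.25 / 0.0894 = 2.795. Power is Φ(2.795 − 1.960) = 79.8%.
- A one-sided test would give 398, so two-sided 5% is what the plan used.

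The calculation is right for self-management, and it uses the whole 5% on that outcome.

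**2. If any one of the three counts as success.** With no true effect on any outcome:

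| Correlation between tests | At least one significant, either direction | At least one significant in favour of the intervention |
|---|---|---|
| 0 | 1 − 0.95³ = 14.3% | 1 − 0.975³ = 7.3% |
| 0.3 | 13.6% | 6.8% |
| 0.5 | 12.5% | 6.3% |
| 0.8 | 9.9% | 4.9% |

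The rows with positive correlation come from simulation. The upper limits under any dependence are 3 × 5% = 15% and 3 × 2.5% = 7.5%. For a single test the two figures would be 5% and 2.5%.

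**3. If all three are required.** The error rate is then at most 5%, but power falls. Suppose each outcome had 80% power, which the protocol claims only for self-management. Joint power is then 0.8³ = 51% for independent tests and 61% at correlation 0.5.

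Blood pressure control may well fall short of 80%. The Discussion reports control between 51% and 91% across practices. Taking control-arm rates from that range, with 187.5 completers per arm and no baseline adjustment, power for a 5-point gain is 16% at 51%, 21% at 75% and 50% at 91%. The 5-point gain and the 75% rate are illustrations and are not protocol figures.

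**4. What an equal split of alpha would cost.** At 0.05 / 3 = 0.0167 the critical value is 2.394. Power for self-management at N = 500 becomes Φ(2.795 − 2.394) = 65.6%. Restoring 80% takes 252 completers per arm, and 504 / 0.75 = 672 patients.

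**The case against.** The best defence is that the three outcomes are separate questions, one clinical and two patient-reported, each with its own answer and no overall verdict. The protocol never speaks of a single positive-trial verdict. On that reading 5% is the right error rate for each question and 80% is the right power for the one that was sized. This stands as a possible reading. The Aims and Outcomes sections do not exclude it, but they do not adopt it either, so the ambiguity remains.

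A second defence is that a multiplicity or interpretation rule may sit in the separate analysis plan. It may, and its absence there cannot be claimed. But the protocol itself fixes three equal primaries, one 5% level and a sample size at the full 0.05. An alpha split in the analysis plan, for example, would have to be reconciled with both the Analysis and Sample size sections.

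Three stronger readings might be inferred, and the documents do not support them:

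- **That the chance of a false positive trial is 14%.** That figure counts significant differences in both directions, including those against the intervention, and it applies only under the any-one reading. In favour of the intervention the figure is about 7%.
- **That the sample size is wrong, or treats self-management as the only primary outcome.** The size reproduces. The phrase in the Sample size calculation can simply identify which of the three was sized.
- **That the documents dictate a full testing order.** Self-management has a claim to come first because the trial was sized on it. Nothing places quality of life ahead of blood pressure, which the Outcomes section in fact lists first.

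**Conclusion.** The point holds as an unresolved ambiguity with measurable consequences, and not as an error in any stated figure. Under the any-one reading, the chance of at least one false significant primary result is up to about 14% in either direction and about 7% in favour of the intervention. Positive correlation between the tests lowers both. Under the all-three reading, joint power is 51% to 61% on the generous assumption of 80% for each outcome, with correlation from 0 to 0.5. The plan's 5% and 80% are sound only if self-management is the first confirmatory test, or if each outcome is reported separately with no overall claim. The protocol does not say that either applies.

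This should be fixed but is not a fatal defect: wording alone resolves it, one legitimate reading leaves the figures intact, and the analysis plan has not been seen.

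**What to change.** Before analysis, amend the Outcomes, Sample size calculation and Analysis sections together:

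- Make self-management ability, the outcome the trial was sized on, the first confirmatory test at two-sided 5%.
- Test health-related quality of life and blood pressure control confirmatorily only if self-management is significant. Use either a fixed order or Holm's procedure between the two, chosen and justified by the sponsor.
- Report all three estimates with 95% confidence intervals whatever the test results.
- State that the 80% power applies to self-management only.
- Bring the separate analysis plan into line with the same rule.

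The cost is wording. The sample size does not change, and the full 5% and 80% stay with self-management, unlike an equal three-way split, which would cut its power to about 66% or require 672 patients. The drawback is that no confirmatory claim on quality of life or blood pressure could be made if self-management is not significant. The Trial status section says recruitment was still under way when the protocol was submitted, so at that point the rule could still be set ahead of the analysis.
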